### Follow-up evaluation

Patients are assessed at baseline, after completion of the intervention period at 5 weeks, and at 3 and 12 months after inclusion to assess the long term outcome of the intervention. An overview of the outcome measures is given in Table 3.

**Table 3 T3:** Primary and secondary outcome measures

Primary Outcomes	Measurement	Follow up
Shoulder pain and disability index (SPADI)	13 items (5 for pain, 8 for function) scored on a 100 mm visual analogue scale	baseline; 5 weeks; 3, 12 months

Patients' global impression of change	Ordinal scale (1-much worse, 2-slightly worse, 3-no change, 4-slightly better, 5-much better)	5 weeks; 3, 12 months

**Secondary Outcomes**	**Measurement**	**Follow up**

Generic patient-specific scale	11 point visual numeric rating scale (end descriptors of 0 = impossible to do, 10 = no difficulties at all)	baseline; 5 weeks; 3, 12 months

Average weekly pain score	11 point visual numeric rating scale (end descriptors of 0 = no pain, 10 = worst pain possible)	baseline; 5 weeks; 3 months

Patients' satisfaction with treatment	11 point visual numeric rating scale (end descriptors of 0 = completely dissatisfied, 10 = completely satisfied)	5 weeks

Kinesiophobia/Fear avoidance beliefs	Modified fear avoidance beliefs questionnaire (FABQ)	Baseline

Catastrophizing	Pain catastrophizing scale (PCS)	Baseline

Patients' expectancies of treatment effect	One modified question from the Credibility/Expectancy Questionnaire (CEQ)	Baseline

Compliance	Shoulder log book: Attention of treatment sessions and completion and frequency of home exercises	5 weeks; 3, 12 months

Costs	Cost diary: Disease specific healthcare utilization, days of sick leave, drug use, paid help	5 weeks; 3, 12 months

### Sample size

Sample size for this trial is based on an expected difference between groups of a 13 points reduction of the SPADI score. The statistical level of significance was set to alpha = 0.05, statistical power to 80%, and a 15% drop out rate was expected. The assumed standard deviation was set to 20 points based on the results of other studies [117-120]. Power calculations resulted in an estimated sample size of 90 participants (45 per group) to detect a 13 points difference in SPADI score. The minimum clinically important change is set to an 11 points improvement in total SPADI score [93].

### Data analysis

First, descriptive statistics for demographical characteristics of the whole group will be used. Second, descriptive statistics for demographical and clinical characteristics, for baseline results of outcome measures and other potential confounding variables for the intervention group and control group will be used. Differences will be calculated for within-groups results and between-groups comparisons. Results will be calculated according to the "intention-to-treat principle". Between groups-analysis will include differences between baseline and follow up measurements for each clinical outcome measure used, their standard deviations and 95% confidence intervals. Additionally mixed models for the long term follow ups will be used. Influence of baseline differences for outcome measures will be assessed in a multivariable linear regression analysis. Statistical significance is set to p ≤ 0.05, clinical importance will be judged by the lower 95% confidence interval which equals the minimum effect size.

An economic evaluation will compare costs of both treatment options from a societal perspective.

Resources recorded in the shoulder log book will be valued using published prices for medical costs. Costs for over the counter drugs, aids, and paid help will be reported directly by the participants in their log-books.

Productivity costs resulting from loss of paid labor will also be calculated by applying the friction costs method, which limits the period of production loss to the time during the work of the person is not replaced.

Between-group differences in outcomes of mean total costs were analyzed by Student's *t*-tests for unpaired observations.

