### Recruitment of participants

The proposed trial will be embedded in the normal daily process of selected physiotherapy clinics in Germany. Participants will be identified by physiotherapy referrals and by research physiotherapists. If a patient agrees to participate, the research therapist will check eligibility criteria. If eligibility is confirmed, informed consent will be asked. Participants will then undergo baseline assessment including some questionnaires and a standardized clinical examination protocol for the shoulder complex, the cervical and upper thoracic spine.

An inclusion period of eighteen months is thought to be sufficient to recruit the number of participants needed for this study.

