### Randomization and allocation concealment

After informed consent and baseline assessment participants will be randomized to either SEP or IP using block allocation of six. To guarantee allocation concealment, therapists will be informed about allocation after the participant completed all baseline measurements and gave informed consent, prior to first treatment by the Department of Epidemiology, Maastricht University.

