Exercises of the "core program" are introduced and instructed to the patient in detail first, and if patients show good progression, exercises from the pool of "additional exercises" can be added. At home exercises are realized with the help of a PINOFIT rubber band (Pino GmbH, Hamburg, Germany) which allows dynamic resistance and is easy to use. It is available from very light resistance to heavy resistance and allows the therapist to progressively adapt resistance to the physical capacity of the patient. Patients are supervised during their contact sessions; their exercise program is monitored, controlled and adapted if necessary. Physiotherapists are allowed to adapt the SEP individually to each patient with respect to the situation of the patient. Therapists who deliver the treatment for the control group remain blinded to the clinical examination results to prevent inadvertent contamination of the SEP.

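### The sample size and the stated between-group intervals make no allowance for the treating therapist, and the article does not say whether therapists work in one arm or both; if in one arm only, the intervals would be too narrow

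*Protocol article*

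**What the plan says.** Under Interventions, every participant has two contact sessions a week for five weeks with a physiotherapist. Under Intervention group, individualized physiotherapy (IP) is six to ten sessions built on the clinical examination findings, guided by a decision tree and manual-therapy concepts. Under Control group: "Therapists who deliver the treatment for the control group remain blinded to the clinical examination results to prevent inadvertent contamination of the SEP". The Discussion repeats this rule as protection against performance bias.

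On setting, Recruitment of participants says: "The proposed trial will be embedded in the normal daily process of selected physiotherapy clinics in Germany". On allocation: "participants will be randomized to either SEP or IP using block allocation of six". Neither section gives the number of clinics or therapists, and no section says whether a therapist treats patients in one arm or in both.

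Sample size: "Sample size for this trial is based on an expected difference between groups of a 13 points reduction of the SPADI score". Also: "The statistical level of significance was set to alpha = 0.05, statistical power to 80%, and a 15% drop out rate was expected", and "The assumed standard deviation was set to 20 points based on the results of other studies". The result is 45 per group.

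The Data analysis section describes the comparison as follows: "Between groups-analysis will include differences between baseline and follow up measurements for each clinical outcome measure used, their standard deviations and 95% confidence intervals". It adds mixed models for the long-term follow-ups without giving their random effects, and judges clinical importance by the lower 95% limit.

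**The concern.** Patients of one therapist share that therapist's skill, style and caseload, so their outcomes may be correlated. This is plausible here because IP rests on clinical reasoning and manual technique, and the section on the main contrast between the groups counts clinical experience as part of the intervention.

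Whether the correlation harms the comparison depends on staffing. If each therapist works in one arm only, differences between therapists become part of the difference between arms, and a standard error computed from individual patients leaves that variation out. The 5% significance rule and the lower-limit rule would then both be too lenient. The mixed models are announced only for the long-term follow-ups, so the stated plan does not place the 5-week comparison in them.

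**Working it through.** **1. Reproduce the plan's figure.** Inputs from Sample size: difference 13, SD 20, alpha 0.05 (two-sided, which reproduces N), power 80%, dropout 15%.

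n per arm = 2 × [20 × (1.960 + 0.842) / 13]² = 37.15, so 38. Inflated: 38 / 0.85 = 44.7, so 45 per arm and 90 in total, as stated. This is the formula for independent patients, with nothing left over for clustering.

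**2. Interval under independence.** SE = 20 × √(2/38) = 4.59 points; half-width = 1.96 × 4.59 = 9.0 points. Power = Φ(13/4.59 − 1.96) = 0.81 (0.80 by t-test).

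**3. Therapists nested in arm.** The documents give neither the number of therapists per arm (k) nor the ICC, so both are assumed and shown as a range. Equal caseloads, the same ICC in both arms and a total SD of 20 are also assumed.

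- Patients per therapist: m = 38/k
- Design effect: DE = 1 + (m − 1) × ICC
- True half-width: 9.0 × √DE
- Real type I error of the unadjusted test: 2 × [1 − Φ(1.96/√DE)]
- Power: Φ(13/(4.59 × √DE) − 1.96), and again from the noncentral t with 2(k − 1) degrees of freedom

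| k per arm | ICC | m | DE | √DE | Half-width | Type I error | Power, normal | Power, t |
|---|---|---|---|---|---|---|---|---|
| 10 | 0.01 | 3.8 | 1.03 | 1.01 | 9.1 | 5.3% | 0.80 | 0.75 |
| 8 | 0.05 | 4.8 | 1.19 | 1.09 | 9.8 | 7.2% | 0.74 | 0.68 |
| 5 | 0.02 | 7.6 | 1.13 | 1.06 | 9.6 | 6.5% | 0.76 | 0.65 |
| 5 | 0.05 | 7.6 | 1.33 | 1.15 | 10.4 | 8.9% | 0.69 | 0.58 |
| 3 | 0.05 | 12.7 | 1.58 | 1.26 | 11.3 | 11.9% | 0.62 | 0.41 |
| 3 | 0.10 | 12.7 | 2.17 | 1.47 | 13.2 | 18.3% | 0.49 | 0.32 |

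For k = 5 and ICC 0.05: DE = 1 + 6.6 × 0.05 = 1.33, √1.33 = 1.153, and 8.99 × 1.153 = 10.4. The lower limit therefore sits about 10.4 − 9.0 = 1.4 points too high. To restore the planned power by the normal approximation, with m held at 7.6, takes 38 × 1.33 = 50.5, so 51 per arm; 51/0.85 = 60 per arm, 120 in total.

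**4. Therapists balanced across both arms, no therapist-by-treatment interaction.** The therapist component cancels from the contrast, so the true SE is 4.59 × √(1 − ICC). At ICC 0.05 the factor is √0.95 = 0.975, and a half-width of 8.99 × 0.975 = 8.8 is enough. The unadjusted 9.0 is slightly too wide.

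**The case against.** A reader might infer that the blinding rule implies a separate team of therapists for each arm. It does not. The rule applies patient by patient: whoever treats a control patient must not know that patient's findings. A therapist who works in both arms can meet it if a colleague did the examination. The Interventions section speaks of all physiotherapists being trained, without naming arm-specific teams, and the allocation is disclosed participant by participant. Nesting is a natural reading, but only a reading, and without it the claim that the intervals are too narrow fails.

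A reader might also infer that the plan declares patients independent. It does not: Data analysis lists what will be reported and leaves the structure of the mixed models open. Random-effect detail commonly sits in an analysis plan, so its absence from an article is no fault. Nor does possible clinic imbalance bias the comparison. The article gives a block size and is silent on stratification, and under individual randomisation a chance difference in clinic mix is ordinary sampling variation.

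The safeguards also count: a common international qualification, training, a written manual, structured forms, check lists, monthly meetings, audits and the decision tree should all keep the ICC down.

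Two things remain. The sample size calculation is fully stated and reproduces under independence, and staffing of the arms is a design matter. A later analysis plan can add a term to a model, but it cannot recover power missing from 90 participants, or a therapist's identity that was never recorded. Further, the balanced case is harmless only without a therapist-by-treatment interaction, which cannot be taken for granted when one arm depends on therapist skill.

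**Conclusion.** The point holds in conditional form. Neither the sample size nor the stated between-group intervals allow for the therapist, and the article leaves open the fact that decides whether this matters.

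Under nesting with a positive ICC, the intervals and the lower-limit rule are too favourable. The size ranges from negligible (10 therapists per arm, ICC 0.01: type I error 5.3%) to substantial (3 per arm, ICC 0.10: 18.3%). A middle case of 5 per arm and ICC 0.05 gives about 9%. Under balanced staffing without interaction the error is small and runs the other way. All of these rest on assumed therapist numbers and ICCs.

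The documents do not support an unconditional statement that the intervals are too narrow. This is worth correcting because the correction is cheap and conclusions hang on the interval, but it does not invalidate the trial.

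**What to change.** - State how many therapists there are and whether each treats one arm or both.
- Record the treating therapist and the clinic for every participant, including those already enrolled (the Results section dates the start of inclusion to April 2010).
- At all time points, including 5 weeks, take the between-group difference and its 95% interval from a model with a random therapist effect (nested in arm if so staffed, with a small-sample degrees-of-freedom correction) and clinic as a covariate. Report the unadjusted interval alongside.
- If therapists are nested, say in the report that therapist and treatment cannot be fully separated. The random effect corrects the width of the interval; it does not remove the particular therapists' skill from the contrast.
- Optionally, stratify the remaining allocation by clinic. This serves precision only.

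Cost: two recorded variables and some analysis wording. The real downside arises under nesting with few therapists: the interval widens, the therapist variance is poorly estimated, and the honest power is below the stated 80% (about 0.58 to 0.69 at 5 per arm and ICC 0.05). The model does not cause that loss; it makes it visible.

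### The SPADI comparison rests on change from baseline, with no lead analysis named; a baseline-adjusted lead model would be more precise at almost no cost

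*Protocol article*

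**What the plan says.** The Data analysis section of the protocol article describes three routes to a treatment effect on a continuous outcome such as SPADI.

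- Change from baseline, reported with SDs and 95% confidence intervals: "Between groups-analysis will include differences between baseline and follow up measurements for each clinical outcome measure used".
- A longitudinal model: "Additionally mixed models for the long term follow ups will be used".
- A regression: "Influence of baseline differences for outcome measures will be assessed in a multivariable linear regression analysis".

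The section does not say which of these carries the conclusion. It commits to intention-to-treat, sets significance at p ≤ 0.05 and judges clinical importance on the lower 95% confidence limit.

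Table 3 has SPADI measured at baseline, 5 weeks, 3 months and 12 months. No visit is named as primary.

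The Sample size section bases 90 participants (45 per group) on an "expected difference between groups of a 13 points reduction of the SPADI score". It adds: "The statistical level of significance was set to alpha = 0.05, statistical power to 80%, and a 15% drop out rate was expected". On variability it says: "The assumed standard deviation was set to 20 points based on the results of other studies". It does not say whether this is the SD of a score at one visit or of the change from baseline.

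**The concern.** Baseline SPADI is collected from everyone and usually predicts follow-up SPADI. Subtracting it fixes the coefficient on baseline at 1. Estimating the coefficient, as ANCOVA does, removes at least as much residual variance in large samples, and usually more. The plan gives the subtraction the descriptive detail (SDs and intervals). It words the adjusted analysis as a check on baseline differences rather than as the estimate of the treatment effect.

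Two things are at stake. One is interval width, which feeds directly into the rule for clinical importance. The other is clarity: change score, regression and mixed model can give three different estimates and p-values for the same primary outcome, and the text does not say which one decides.

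**Working it through.** **Inputs.** From the Sample size section: difference 13, SD 20, alpha 0.05 (two-sided assumed, since it reproduces the stated N and one-sided does not), power 80%, drop-out 15%, 45 per arm. The correlation r between baseline and follow-up SPADI is not in the document, so r = 0.3 to 0.7 is assumed. Equal SDs at baseline and follow-up are also assumed unless stated otherwise.

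**Step 1: the plan's own figure.** n per arm = 2 × 20² × (1.96 + 0.842)² / 13² ≈ 37.2, rounded up to 38. Then 38 / 0.85 = 44.7, rounded up to 45 per arm, or 90 in total. The stated N is reproduced, and 38 completers per arm is the basis for what follows.

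**Step 2: precision.** For a single-score SD σ:

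- change-score variance = 2σ²(1 − r)
- ANCOVA variance = σ²(1 − r²)
- ratio = (1 + r)/2, that is 0.65 at r = 0.3, 0.75 at 0.5 and 0.85 at 0.7.

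**Step 3: interval width if 20 is the SD of change.** Half-width = t × SD × √(2/38), with t ≈ 1.993 on 74 df and √(2/38) = 0.2294. The ANCOVA SD is 20 × √((1 + r)/2).

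| Analysis | SD | Half-width | Lower limit if the estimate is 13 |
|---|---|---|---|
| Change score | 20.00 | 9.1 | 3.9 |
| ANCOVA, r = 0.3 | 16.12 | 7.4 | 5.6 |
| ANCOVA, r = 0.5 | 17.32 | 7.9 | 5.1 |
| ANCOVA, r = 0.7 | 18.44 | 8.4 | 4.6 |

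**Step 4: power under each reading of the SD.** Two-sided t-test, difference 13, 38 per arm.

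| r | Change score, 20 = score SD | ANCOVA, 20 = score SD | Change score, 20 = change SD | ANCOVA, 20 = change SD |
|---|---|---|---|---|
| 0.3 | 65.7% | 83.4% | 79.9% | 93.4% |
| 0.4 | 72.3% | 86.2% | 79.9% | 91.7% |
| 0.5 | 79.9% | 89.8% | 79.9% | 89.8% |
| 0.6 | 87.8% | 93.8% | 79.9% | 87.8% |
| 0.7 | 95.1% | 97.5% | 79.9% | 85.8% |

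The 79.9% is the t-based value; the normal approximation gives 80.9%, so it counts as meeting the target. The change score falls short only in the first two rows of the first power column. ANCOVA exceeds 80% in every cell.

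**Step 5: sensitivity to equal SDs.** Take an assumed baseline SD of 16, follow-up SD of 20 and r = 0.5. Change variance = 256 + 400 − 2 × 0.5 × 16 × 20 = 336. ANCOVA variance = 400 × 0.75 = 300. The ratio is 0.89 rather than 0.75, with power about 86% against 90%. With baseline SD 14 and r = 0.7, both variances are 204 and the gain vanishes.

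**The case against.** **The power target may already be met.** The sample size is framed as a difference in reduction, which is naturally read as a change, so 20 can be read as the SD of change. The planned analysis then has about 80% power at any r. This stands. A reader might infer that the trial is underpowered, but that needs both a single-score SD and r below 0.5, and the document settles neither.

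**The loss of precision is not universal.** The (1 + r)/2 ratio needs equal SDs, and step 5 shows that the advantage can shrink to nothing. Excluding patients with average pain of 8/10 or more could narrow the baseline spread. This stands too: the supportable statement is that adjustment is never less precise in large samples, not that it is always better.

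**Adjustment is already planned.** The regression is stated without any trigger, so reading it as a reaction to observed imbalance would be inference. Regressing change on arm and baseline would give the same arm estimate as ANCOVA. The text nevertheless words it as an assessment of baseline differences and gives it no priority. If ANCOVA was meant as the lead, one sentence would say so.

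**The ranking may be in an analysis plan.** An unseen analysis plan may rank the three analyses. That is possible. The point here is limited to how the article frames the comparison that it does describe.

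**Non-attenders.** A reader might infer that change scores discard the patients behind "a 15% drop out rate was expected". The documents do not support this. The 90 already allows for that loss, no complete-case rule is written, intention-to-treat is stated, and the long-term mixed models can use partial follow-up. A change score does need a value at its visit, but handling of missing values is commonly left to the analysis plan.

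**Conclusion.** The point holds as one of efficiency and clarity, not of bias. The protocol describes the between-group comparison through change scores, gives baseline adjustment a side role and names no lead among three analyses.

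With equal SDs and r of 0.3 to 0.7 (both assumed), adjustment would cut the variance by 15% to 35%. With a change SD of 20 and 38 per arm, it would narrow the half-width by about 0.7 to 1.8 points. At an estimate of 13, that moves the lower limit from 3.9 to between 4.6 and 5.6. The limit remains well below the 11-point threshold for important change, so adjustment helps under the lower-limit rule but does not by itself decide it.

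The power result is conditional. If 20 is a score SD and r is below 0.5, the change score gives 66% at r = 0.3 and 72% at r = 0.4, against 83% and 86% with ANCOVA. If 20 is the SD of change, the planned analysis has about 80% and ANCOVA has 86% to 93%.

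**What to change.** 1. Name one lead analysis for SPADI: a linear mixed model of the 5-week, 3-month and 12-month scores on arm, visit, arm-by-visit and baseline SPADI. Read the arm difference at each visit with its 95% interval, and designate one visit as primary, because the protocol names none.
2. Use the same approach for the patient-specific scale at all three follow-up visits. For weekly pain use 5 weeks and 3 months only, because Table 3 has no 12-month value.
3. Keep change scores as description. The separate regression on baseline differences then becomes unnecessary for these outcomes.
4. State in the Sample size section whether the SD of 20 is for a single score or for change.

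This model uses patients with at least one follow-up value, so those with none still need a stated approach in the analysis plan. The cost is wording only: no extra patients, visits or measurements.

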### Outcome measures

Selection criteria for the outcome measures used in this study were their reliability and validity in relation to the study population, and also their sensitivity to detect change statistically, whether it is relevant to the patient or clinician or not. Another important criterion was their practical applicability in a clinical setting. The main focus is on pain and functioning. Primary outcome measures will be as follows:

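### SPADI and PGIC are both primary at three follow-ups under one 0.05 threshold, but no primary visit, order or success rule is fixed, and the sample size names no visit

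*Protocol article*

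**What the plan says.** All references are to the Protocol article.

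- **Outcome measures.** The list opens in the plural, "Primary outcome measures will be as follows", and contains two items: SPADI (numbered 1) and PGIC (numbered 2, an ordinal rating that is dichotomized).
- **Follow-up evaluation and Table 3.** "Patients are assessed at baseline, after completion of the intervention period at 5 weeks, and at 3 and 12 months after inclusion". Table 3 lists all three follow-ups for both primary outcomes and marks none as primary.
- **Sample size.** "Sample size for this trial is based on an expected difference between groups of a 13 points reduction of the SPADI score". The other inputs are an alpha of 0.05, 80% power, 15% dropout and an SD of 20 points taken from earlier trials. The result is 90 participants, 45 per group. No visit is attached to the 13 points.
- **Data analysis.** Between-group comparisons of change from baseline to follow-up are planned for every clinical outcome, with confidence intervals. Mixed models for the long-term follow-ups come in addition. One threshold is given: "Statistical significance is set to p ≤ 0.05". The same sentence adds that clinical importance will be judged from a confidence limit.
- **Results.** First results are expected in 2012 and long-term results in 2013.

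**The concern.** Two outcomes at three visits give six primary between-group comparisons, and the text does not say which of them answers aim (a). Two things follow.

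First, the design figures are not anchored. An alpha of 0.05 and a power of 80% describe one SPADI comparison, but the reader cannot tell whether it is at 5 weeks, 3 months or 12 months.

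Second, conflicting results have no rule. If SPADI were significant at 5 weeks and not at 12 months, or PGIC were significant and SPADI not, the article would support more than one conclusion. Staged reporting makes this a practical matter: early visits may be published before the 12-month data exist, and nothing says which release decides. If any favourable result could then carry the claim, the error rate of that claim would be well above the nominal level.

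**Working it through.** **1. The plan's own sample size.** Inputs from Sample size: difference 13, SD 20, alpha 0.05 (taken as two-sided, since sidedness is not stated), power 80%, dropout 15%.

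n per arm = 2 × (1.960 + 0.842)² × (20/13)² = 2 × 7.85 × 2.367 ≈ 37.2, so 38 completers. 38 / 0.85 = 44.7, so 45 per arm and 90 in total. This matches the article and confirms that N is sized for one two-sided test at 0.05.

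**2. Counting the comparisons.** 2 primary outcomes × 3 follow-ups = 6.

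**3. Independent tests.**
- At least one of six significant in either direction: 1 − 0.95⁶ = 0.265.
- At least one of six significant in favour of individualized physiotherapy: 1 − 0.975⁶ = 0.141. The single-test comparator here is 0.025.
- SPADI alone at three visits, either direction: 1 − 0.95³ = 0.143.

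**4. Correlated tests.** The article gives no correlations, so they were varied as assumptions. Six standard normal statistics were simulated under no effect (400,000 draws, cut-off 1.96). The correlation between different outcomes at different visits was the product of the time and outcome correlations.

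| Time corr. | Outcome corr. | Any of six, either direction | Any of six, favouring IP | SPADI only, three visits |
|---|---|---|---|---|
| 0.3 | 0.3 | 24.8% | 12.7% | 13.6% |
| 0.4 | 0.3 | 24.0% | 12.2% | 13.1% |
| 0.5 | 0.5 | 22.0% | 11.1% | 12.6% |
| 0.7 | 0.7 | 17.7% | 8.8% | 10.9% |
| 0.8 | 0.8 | 14.9% | 7.5% | 9.9% |

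Time correlations of 0.4-0.7 with outcome correlations of 0.3-0.7 therefore give about 18-24% in either direction and 9-12% in favour of individualized physiotherapy. Higher correlations lower the figure further: with one common correlation of 0.9 among all six tests it is 10.9%.

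**5. A different success rule.** Suppose both outcomes had to be significant at the same visit, at any of the three visits. Over time and outcome correlations of 0.3-0.8 the error is then about 1-6%, so there is little or no inflation.

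**6. Effect of possible remedies on power.** With 38 completers per arm:
- One SPADI test at 0.05: the standard error is 20 × √(2/38) = 4.59 and 13/4.59 = 2.83. Power is 80.9% by the normal approximation and 79.9% by the t-test.
- Bonferroni over six (0.05/6 = 0.0083): 57.7% by the normal approximation and 55.1% by the t-test. Restoring 80% needs 58 completers per arm, and 58/0.85 = 68.2, so 69 per arm or 138 in total.
- A fixed sequence starting with one SPADI comparison: the first test keeps its full 0.05 and about 80% power.

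**The case against.** The strongest objection is that the article never says any one of six results is enough. It sets a threshold and is silent on how results combine. A reader might infer that the plan carries an 18-24% chance of falsely declaring individualized physiotherapy effective, where 5% was intended. The text does not support that, for three reasons: the any-of-six rule is an assumption, the correlations are assumptions, and 18-24% counts significance in either direction. The matching figure for a false favourable result is 9-12%, and its comparator is 2.5%. All of this stands, and the figures are stated conditionally for that reason.

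Other points carry less weight:
- SPADI is listed first and alone drives the sample size. This hints at precedence but is not a stated hierarchy, and it does not choose a visit. SPADI alone at three visits still gives about 10-14%.
- The mixed models might combine visits. They are planned in addition to the between-group comparisons, cover only the long-term follow-ups, and name no deciding contrast.
- Clinical importance is to be judged from a confidence limit. This is a further criterion for interpretation, but it does not say at which visit or for which outcome it applies.
- Multiplicity adjustment is commonly left to an analysis plan, and one may exist. The absence of an adjustment is therefore not the point here. Which comparison the primary question and the sample size refer to is a design matter that the article fixes incompletely.

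**Conclusion.** The concern holds as a structural one. Two primary outcomes at three visits share one threshold, and the text does not identify the comparison to which the 5% and the 80% apply. The calculation behind N = 90 is correct and not in dispute.

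The size depends on the success rule. If any of the six two-sided tests may support the conclusion, at least one false significant primary result has a chance of about 15-26% over the range from correlations of 0.8 to independence. It is lower still only if all six tests are very highly correlated. The relative inflation for a false favourable result is about 3.5 to 5 times (8.8/2.5 to 12.2/2.5) at the moderate correlations. If both outcomes had to succeed at one visit, the inflation would largely vanish. That the article allows such different readings is the defect; no single error rate can be assigned to it.

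**What to change.** Before any look at outcomes by group, amend three sections:

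- **Outcome measures:** name total SPADI at one visit as the primary comparison. The sponsor should choose the visit, for example 5 weeks (end of the contact phase) or 3 months (end of the home programme); the document does not settle it.
- **Sample size:** state that the 13 points, alpha 0.05 and 80% power refer to that comparison.
- **Data analysis:** test that comparison at two-sided 0.05. Test PGIC at the same visit, also at 0.05, only if SPADI is significant. Report the remaining visits as secondary estimates with confidence intervals and without confirmatory claims.

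This costs a few sentences and neither participants nor data. It holds the error over the two confirmatory tests at 5% and leaves N at 90. The price is that significance at a non-primary visit alone, or on PGIC alone, no longer counts as confirmatory.
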